#### (2) Type I error control for the re-estimation of sample size based on PFS

The safety analysis, re-estimation of sample size, and efficacy analysis will be conducted by the iDMC. The re-estimation of sample size based on PFS is planned after 50% of the planned PFS events (174 cases). At the same time, a safety analysis will be performed. The interim analysis will be conducted by iDMC.

The non-blind re-estimation of sample size is a procedure with multiple tests, with a concern on data dependency in different stages, which would increase the inflation of the type I error rate. To address this problem, P values in two stages will be combined using the MSP.

According to the preliminary test, in the PFS interim analysis based on the re-estimation of sample size, the one-side significance level is set as  $\alpha_1=0.005$ , and the futility boundary is set as  $b_1=0.45$  in the first stage; the one-side significance level is set as  $\alpha_2=0.2050$  in the secondary stage. No early discontinuation of the study due to PFS efficacy would be considered.

- Either  $P_1 \leq \alpha_1$  or  $P_1 > \alpha_1$ , once  $P_1 \leq b_1$ , the trial will continue to the second stage, without early discontinuation due to PFS efficacy;

- If  $P_1 > b_1$ , the trial will terminate early for futility;
- If the trial could proceed into the second stage,  $P_1 + P_2 \leq \alpha_2$  [that is, adjust P value =  $\alpha_1 + (P_1 + P_2)(b_1 - \alpha_1) - 1/2 (b_1^2 - \alpha_1^2) \leq 0.025$ ], the between-group difference in PFS will be considered as statistically significant.

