**Figure S4. Fixed-sequence test for multiple testing between treatment groups.**

A fixed-sequence test was used for multiple testing between treatment groups. Testing begins with the first hypothesis, H1, and each test is carried out without a multiplicity adjustment, provided that significant results are observed in all preceding tests. The fixed-sequence procedure controls the family-wise error rate because, for each hypothesis, testing is conditional upon rejecting all hypotheses earlier in the sequence.  $P_1$ =the one-side  $P$  value in the interim analysis;  $P_2$ =the one-side  $P$  value in the final analysis. A two-sided test with a significance level of  $\alpha=0.05$  was used for secondary efficacy endpoints and safety analysis. Two-sided  $P\leq 0.05$  was considered statistically significant with a 95% CI.

OS=overall survival; PFS=progression-free survival.

[figure not shown]

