#### **4.1.4 Determination of Total Sample Size**

Considering the sample size estimation in sections 4.1.2 and 4.1.3, 738 subjects will be finally enrolled in this trial and be randomly assigned (1:1:1) to three groups. The interim analysis and final analysis for PFS are conducted for this trial after 174 and 347 cases of the planned PFS events, respectively. The interim analysis and final analysis for OS are performed for this trial following 348 and 497 cases of the planned OS events, respectively.

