### 13.2.2 Size of a Test

#### (1) Type I error control in the multiple-group comparison

There are 3 arms in this trial:

Intervention arm 1: TQB2450, Anlotinib, Carboplatin, and Etoposide

Intervention arm 2: TQB2450 placebo, Anlotinib, Carboplatin, and Etoposide

Control arm: TQB2450 placebo, Anlotinib placebo, Carboplatin, and Etoposide

The primary efficacy endpoints of this trial are PFS and OS. In this trial, a fixed-sequence test will be used for comparisons between treatment groups:

- a) The PFS between intervention arm 1 and the control arm (PFS1) will be first tested with the two-sided significance level of 0.05 (one-side, 0.025). If PFS1 is statistically significant, the OS between intervention arm 1 and the control arm (OS1) will be then tested.
- b) If OS1 is statistically significant, the PFS between intervention arm 2 and the control arm (PFS2) will be tested.
- c) If PFS2 is statistically significant, the OS between intervention arm 1 and intervention arm 2 (OS3) will be then tested.
- d) If OS3 is statistically significant, the OS between intervention arm 2 and the control arm (OS2) will be tested.

The overall significance level is set as 0.05 at two-side (one-side, 0.025). Familywise error rate (FWER) will be controlled by the fixed order test when each hypothesis presupposes the rejection of all previous tests.

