### (3) Type I error control for interim efficacy analysis based on OS

One interim analysis for OS is planned for this trial after 70% of the planned OS events (348 cases). If expected efficacy is observed, early declaration of the trial due to efficacy would be considered. The interim analysis will be conducted by iDMC.

Type I error will be controlled by the O'Brien-Fleming spending function approach. According to the O'Brien-Fleming spending function approach, in the interim efficacy analysis based on OS, the one-side significance level is set as  $\alpha_1 = 0.0074$  in the interim analysis and  $\alpha_2 = 0.0228$  in the final analysis.

- In the interim analysis:  $P_1 \leq \alpha_1$ , early declaration of the trial will be considered according to actual results;
- In the final analysis:  $P_2 \leq \alpha_2$ , the between-group difference in OS will be considered statistically significant.

$P_1$  = the one-side P value in the interim analysis;  $P_2$  = the one-side P value in the final analysis;

The tests sequence and type I error in the final analysis are shown in the following figure:

[figure not shown]

A two-sided test with a significance level of  $\alpha=0.05$  will be used for secondary efficacy endpoints and safety analysis. Two-sided  $P \leq 0.05$  will be considered statistically significant with a 95%CI.

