### **13.4 Efficacy Analysis**

#### **13.4.1 Analysis of Primary Efficacy Endpoints**

##### **➤ PFS**

The median PFS will be estimated using the Kaplan-Meier method and presented with the Kaplan-Meier curve.

The comparison of PFS between intervention arms will be performed using a stratified log-rank test. The HR and the corresponding 95%CI will also be provided based on a Cox proportional hazard model, using ECOG PS (0 vs. 1), brain metastases (yes vs. no), and liver metastases (yes vs. no) as concomitant variables. The results of the unstratified log-rank test and results of the Cox proportional hazard model without covariates adjustment will also be provided.

Subgroup analysis of PFS will be performed based on stratification factors.

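### The PFS bound P1+P2 ≤ 0.2050 holds only for independent stage-wise P values, but P2 is not defined for PFS and the only definition in the protocol points to the whole-trial final P value

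*Protocol*

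**What the plan says.** Protocol 13.2.2(1) sets the error budget: "The overall significance level is set as 0.05 at two-side (one-side, 0.025"). PFS1 (intervention arm 1 against control) is tested first, and every later test depends on it.

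Section 13.2.2(2) covers PFS. It names dependence between the data of the two stages as a source of type I error inflation and answers: "To address this problem, P values in two stages will be combined using the MSP". It sets a one-sided first-stage level of 0.005, a futility bound of 0.45 on P1 and a bound of 0.2050 on P1+P2. There is no early stop for PFS efficacy. P1 and P2 are used here but not defined.

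The definition comes in 13.2.2(3), under the OS interim analysis and just above the test-sequence figure, where P2 is "the one-side P value in the final analysis". The legend of Figure S4, which covers the full fixed sequence and abbreviates both OS and PFS, repeats it.

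Section 4.1.4 gives the PFS event counts as running totals: "The interim analysis and final analysis for PFS are conducted for this trial after 174 and 347 cases of the planned PFS events, respectively". Section 13.4.1 describes the test: "The comparison of PFS between intervention arms will be performed using a stratified log-rank test". No second-stage or incremental statistic appears anywhere.

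**The concern.** The method based on the sum of P values has a simple null distribution when P1 and P2 are independent and uniform. For a log-rank test this means P2 must use only the information gained after the interim analysis. Adding two P values does not create that independence. Section 13.2.2(2) names the danger but leaves out the condition that removes it.

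A statistician who looks up P2 in the protocol finds the final-analysis definition, an event total that contains the interim events, and an ordinary stratified log-rank test. The obvious program puts the whole-trial P value into P2. P1 and P2 then share 174 of 347 events and their test statistics have null correlation √(174/347) = 0.71, so 0.2050 is the wrong critical value.

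At stake is the first test of the sequence. If PFS1 is tested above one-sided 0.025, the familywise claim fails at its first step. PFS2 is exposed too, since the section does not confine its rule to PFS1.

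**Working it through.** **Inputs (Protocol).** One-sided α = 0.025 (13.2.2(1)); α1 = 0.005, b1 = 0.45 and bound c = 0.2050 (13.2.2(2)); PFS events 174 and 347 (4.1.4), so t = 174/347 = 0.501. The pairwise counts in 4.1.2 and 4.1.3 give nearly the same fraction: 83/165 = 0.503 and 116/231 = 0.502.

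**1. Reproduce the plan's bound.** Take P1 and P2 independent and uniform. Because b1 = 0.45 exceeds c = 0.2050, the futility bound does not limit the success region, and

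α = α1 + ½(c − α1)² = 0.005 + 0.5 × 0.200² = 0.0250.

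Solving back, c = 0.005 + √(2 × 0.020) = 0.2050. The plan's figure is exactly the bound for independent stage-wise P values.

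This calculation counts P1 ≤ 0.005 as a success in itself. The text does not say that it does. If success needs P1+P2 ≤ 0.2050 in every case, the error is ½ × 0.2050² = 0.0210.

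**2. Same bound, P2 from all 347 events.** Under the null, Z_final = √t × Z1 + √(1−t) × Z2 with Z1 and Z2 independent standard normal. Numerical integration of Pr(P1 + P_final ≤ 0.2050) gives:

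| Basis of P2 | Sum rule only | P1 ≤ 0.005 also counts |
|---|---|---|
| Second stage only | 0.0210 | 0.0250 |
| All events, t = 174/347 | 0.0726 | 0.0729 |
| All events, t = 83/165 | 0.0727 | 0.0730 |
| All events, t = 116/231 | 0.0727 | 0.0729 |

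Four million simulated trials at t = 174/347 gave 0.0726 and 0.0729 with the cumulative P2, and 0.0212 and 0.0252 with the second-stage P2.

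**3. Sensitivity to the information fraction.** With a cumulative P2 and the sum rule only, the error runs from 0.059 at t = 0.3 to 0.085 at t = 0.7. The protocol gives no event total after re-estimation. Assuming totals of 400, 550 or 694 (694 is twice 347) with the interim still at 174, the error is 0.068, 0.060 or 0.055. A larger trial does not cure it.

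**4. Bound that a cumulative P2 would need.** At t = 174/347, one-sided 0.025 needs P1+P2 ≤ about 0.086 (about 0.083 if P1 ≤ 0.005 also counts), not 0.2050.

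**5. One data set, two answers.** Take interim P1 = 0.055 (Z = 1.598) and a whole-trial final P = 0.15 (Z = 1.036).

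- Cumulative P2: 0.055 + 0.15 = 0.205, so PFS is declared significant.
- Second-stage P2: Z_inc = (√347 × 1.036 − √174 × 1.598)/√173 ≈ −0.13, so P2 ≈ 0.55. The sum is about 0.61 and PFS is not significant.

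**The case against.** A reader might infer that the protocol defines the PFS P2 on cumulative data and that the trial therefore runs at a type I error of about 0.07. The documents do not support this.

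- The PFS testing text never calls P2 cumulative. Section 13.2.2(2) speaks of P values in two stages, which most naturally means one per stage.
- The definition of P2 stands in the OS section. Symbols are reused from section to section there: α1 and α2 are 0.005 and 0.2050 for PFS but 0.0074 and 0.0228 for OS. P2 could be local in the same way.
- The figure beneath that definition and Figure S4 itself are not shown, so their labels cannot be checked. Figure S4 also belongs to the supplementary results.
- The constant 0.2050 is the independent-stage bound to the last digit, which is good evidence that a stage-wise P2 was intended. On that reading there is no inflation.
- The construction of a second-stage log-rank statistic is commonly left to the statistical analysis plan, which is not at hand.

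The first four arguments stand against the stronger reading. They do not remove the point. The intention has to be deduced from the constant, while the one definition offered, attached in Figure S4 to a sequence that begins with PFS1, leads the other way. The last argument holds for the formula and the code. It does not cover the meaning of P2, because the protocol itself fixes the bound, the decision rule and the P2 definition, and taken together as written these do not give 0.025.

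**Conclusion.** The point holds as a conflict between a stated threshold and the only stated definition of its input, not as a demonstrated type I error failure. If P2 is taken as that definition reads, on all events to the final analysis, the one-sided error of PFS1 is about 0.073, or 2.9 times the nominal 0.025. If P2 comes from second-stage information only, the error is 0.021 to 0.025 and the claimed control stands.

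The figures rest on the usual large-sample independent-increments behaviour of the log-rank statistic and on an information fraction near 0.50. The direction does not depend on that fraction: every value examined from 0.25 to 0.70 gives at least 0.055. Because the two readings can reverse the verdict on the gatekeeping test, the definition must be settled in the protocol.

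This is separate from the bracketed adjusted-P expression in 13.2.2(2), which gives −0.005 at P1+P2 = 0.2050 and so does not match the bound. Correcting that expression would leave P2 as unclear as before.

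**What to change.** In 13.2.2(2), state that for PFS P1 is the one-sided stratified log-rank P value at the interim analysis and P2 is the one-sided P value from second-stage information only. One way to do so, with d1 and d2 the compared pair's events at interim and final and Z positive in favour of the intervention:

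Z_inc = (√d2 × Z_final − √d1 × Z_interim)/√(d2 − d1), P2 = 1 − Φ(Z_inc).

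Limit the final-analysis definition of P2 in 13.2.2(3) and in the Figure S4 legend to OS, where the O'Brien-Fleming bounds do assume cumulative data. Say also whether P1 ≤ 0.005 alone counts as PFS success, since that separates 0.025 from 0.021.

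The cost is a few sentences in the protocol and a few lines of code, with no extra patients or data. The downside is that the PFS criterion becomes harder to meet than with a cumulative P2.

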#### **4.2 Interim Analysis**

The interim analysis will be conducted by iDMC to assess the risk-benefit in the phase III trial. The iDMC, consisting of two independent oncologists and one independent statistician, is independent of the sponsors and investigators.

The analysis of safety and efficacy and re-estimation of sample size will be performed by iDMC in this trial. The re-estimation of sample size is mainly based on PFS and is planned after 50% of the planned PFS events (174 cases). At the same time, a safety analysis will be performed. If the planned sample size cannot achieve adequate power in the final analysis, the sample size will be increased. In contrast, if obtained power is adequate, the sample size will not be changed. The determinations for sample size are detailed in the iDMC guidelines. In parallel, efficacy analysis for OS is planned in this study after 70% of the planned OS events. If expected efficacy is observed, early declaration of the study due to efficacy would be considered. The interim analysis for OS and the final analysis for PFS will be carried out at the same time, whichever comes later.

Based on the analysis results, IDMC will provide a written recommendation to the sponsor on whether to carry out the trial or to continue the trial after modifying the protocol. The sponsor will make the appropriate decisions on the research project based on IDMC's recommendations, such as

termination of the trial due to safety or lack of efficacy.

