### 13.2.3 Hypothesis

The primary efficacy endpoints of this trial are PFS and OS.

Comparison between groups will be performed using a stratified log-rank test:

➤ PFS hypothesis 1 (Intervention arm 1 vs. Control arm)

$H_{0(PFS1)}$ : PFS in intervention arm 1 = PFS in the control arm, that is,  $S_1(t) = S_2(t)$ ;

$H_{1(PFS1)}$ : PFS in intervention arm 1  $\neq$  PFS in the control arm, that is,  $S_1(t) \neq S_2(t)$ ;

*If the test for PFS does not reject the null hypothesis  $H_{0(PFS1)}$ , all subsequent tests will be terminated; if  $H_{0(PFS2)}$  is rejected, tests will be continued. This result will demonstrate the superiority of PFS in intervention arm 1 compared with the control arm.*

➤ OS hypothesis 1 (Intervention arm 1 vs. Control arm)

$H_{0(OS1)}$ : OS in intervention arm 1 = OS in the control arm, that is,  $S_1(t) = S_2(t)$ ;

$H_{1(OS1)}$ : OS in intervention arm 1  $\neq$  OS in the control arm, that is,  $S_1(t) \neq S_2(t)$ ;

*If the test for OS does not reject the null hypothesis  $H_{0(OS1)}$ , all subsequent tests will be terminated; if  $H_{0(OS1)}$  is rejected, tests will be continued.*

➤ PFS hypothesis 2 (Intervention arm 2 vs. Control arm)

$H_{0(PFS2)}$ : PFS in intervention arm 2 = PFS in the control arm, that is,  $S_1(t) = S_2(t)$ ;

$H_{1(PFS2)}$ : PFS in intervention arm 2  $\neq$  PFS in the control arm, that is,  $S_1(t) \neq S_2(t)$ ;

*If the test for PFS does not reject the null hypothesis  $H_{0(PFS2)}$ , all subsequent tests will be terminated; if  $H_{0(PFS2)}$  is rejected, tests will be continued.*

➤ OS hypothesis 3 (Intervention arm 1 vs. Intervention arm 2)

$H_{0(OS3)}$ : OS in intervention arm 1 = OS in the control arm, that is,  $S_1(t) = S_2(t)$ ;

$H_{1(OS3)}$ : OS in intervention arm 1  $\neq$  OS in the control arm, that is,  $S_1(t) \neq S_2(t)$ ;

*If the test for OS does not reject the null hypothesis  $H_{0(OS3)}$ , all subsequent tests will be terminated; if  $H_{0(OS3)}$  is rejected, tests will be continued.*

➤ OS hypothesis 2 (Intervention arm 2 vs. Control arm)

$H_{0(OS2)}$ : OS in intervention arm 2 = OS in the control arm, that is,  $S_1(t) = S_2(t)$ ;

$H_{1(OS2)}$ : OS in intervention arm 2  $\neq$  OS in the control arm, that is,  $S_1(t) \neq S_2(t)$ ;

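### The PFS futility bound (0.45) lies above the success cut-off (0.2050), so the plan continues, and may enlarge, a trial that can no longer succeed

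*Protocol*

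**What the plan says.** Section 13.2.2 (2) of the protocol sets up a two-stage PFS test with unblinded sample-size re-estimation after 174 PFS events. It says that "P values in two stages will be combined using the MSP". Alpha1 is 0.005 one-sided. For the other two constants, "the futility boundary is set as $b_1=0.45$ in the first stage" and "the one-side significance level is set as $\alpha_2=0.2050$ in the secondary stage".

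Three decision rules follow:
- Any P1 up to b1 takes the trial into stage 2, even when P1 is below alpha1, because "No early discontinuation of the study due to PFS efficacy would be considered".
- If P1 is above b1, "the trial will terminate early for futility".
- After stage 2, PFS is significant if P1 + P2 is at most alpha2. A bracket restates this as an adjusted P value, alpha1 + (P1 + P2)(b1 - alpha1) - (b1² - alpha1²)/2, being at most 0.025.

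Two other places matter. Section 4.2 says: "If the planned sample size cannot achieve adequate power in the final analysis, the sample size will be increased". In section 13.2.3, if the first hypothesis (PFS, arm 1 versus control) is not rejected, "all subsequent tests will be terminated".

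**The concern.** A futility bound should stop a trial whose chance of success has become too small. Here the bound is more than twice the largest P1 that can still succeed. Between the two values the rule requires continuation although conditional power is exactly zero, and extra events cannot raise it. The re-estimation clause points towards more patients in precisely this situation.

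PFS1 is also the gate to OS1, PFS2, OS3 and OS2, so continuing for overall survival does not preserve a confirmatory claim. What is at stake is the enrolment or addition of patients for a confirmatory objective that is already lost, and a written PFS criterion with two versions that disagree.

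**Working it through.** **Inputs.** Section 13.2.2 (2): alpha1 = 0.005, b1 = 0.45, alpha2 = 0.2050, interim at 174 PFS events. Section 4.1.2: HR 0.6, 165 PFS events, about 83 at interim. Section 4.1.3: HR 0.65, 231 PFS events. Section 4.1.1: power 85%.

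**1. The plan's own figures reproduce under the 0.2050 rule.** For b1 at or above alpha2, the MSP type I error, counting P1 ≤ alpha1 as a rejection, is alpha1 + (alpha2 - alpha1)²/2 = 0.005 + 0.200²/2 = 0.0250. If only the sum rule counts, since the trial does not stop for PFS efficacy, it is 0.205²/2 = 0.0210. Power under the sum rule, with two equal independent log-rank stages, is 84.6% (165 events, HR 0.6) and 84.4% (231 events, HR 0.65), against the stated 85%. So 0.2050 is evidently the cut-off on which the design was built.

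**2. The zone that cannot succeed.** Success needs P2 ≤ 0.2050 - P1. For P1 > 0.205 the right-hand side is negative, so no P2 satisfies it. With 83 events, P1 from 0.205 to 0.45 corresponds to an observed interim HR of about 0.835 to 0.973, from exp(-2z/√83) with z = 0.824 and 0.126.

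**3. Chance of landing in it.** With drift m = √(events/4) × |ln HR|, the probability is Φ(0.824 - m) - Φ(0.126 - m).

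| True HR | Interim events, arm 1 + control | m | P(0.205 < P1 ≤ 0.45) |
|---|---|---|---|
| 1.00 | any | 0 | 24.5% |
| 0.60 | 83 | 2.327 | 5.3% |
| 0.60 | 121 (assumed) | 2.810 | 2.0% |
| 0.75 | 83 | 1.310 | 19.5% |
| 0.75 | 121 (assumed) | 1.582 | 15.2% |

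The protocol gives no split of the 174 pooled events by arm. The figure of 121 assumes 246 patients per arm, uniform 12-month accrual, exponential PFS with a control median of 4 months, HRs of 0.60 and 0.65, and no dropout. This gives about 71 control, 50 arm 1 and 53 arm 2 events.

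**4. The bracketed formula at the stated constants.** At P1 + P2 = 0.205 with b1 = 0.45:

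0.005 + 0.205 × 0.445 - (0.2025 - 0.000025)/2 = 0.005 + 0.0912 - 0.1012 = -0.0050.

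This is not a possible P value. The expression integrates up to b1 and is valid only when b1 does not exceed alpha2. Solving it for 0.025 gives a cut-off of (0.020 + 0.1012375)/0.445 = 0.2724. Testing at that cut-off has a true one-sided type I error of 0.2724²/2 = 0.0371, or 0.005 + 0.2674²/2 = 0.0408 if P1 ≤ 0.005 also counts as a win. Even on this reading, P1 between 0.2724 and 0.45 cannot succeed (17.8% with no effect).

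**5. The formula with b1 = 0.205.**

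0.005 + 0.205 × 0.200 - (0.042025 - 0.000025)/2 = 0.005 + 0.041 - 0.021 = 0.0250.

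The two statements of the rule then agree exactly. Power and type I error are as in step 1, because P1 above 0.205 contributes to neither.

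**The case against.** The strongest reply is that nothing inferential is harmed. Under the 0.2050 rule, type I error and power are the same for every b1 of 0.205 or more. No false claim can arise from the zone and no winnable trial is lost. That stands, and it limits the severity.

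A second reply is that the zone is rare if the treatment works as assumed. This also stands: about 2% at HR 0.6 on the likely event count, and 5.3% only on the stand-alone count of 83. The zone becomes common when the effect is weak or absent, which is where a futility rule is meant to work.

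Third, section 4.2 leaves the sample-size decision to iDMC guidelines that are not at hand, and lets the sponsor end the trial for lack of efficacy on iDMC advice. An increase in this zone is therefore permitted by the protocol but not certain. Even so, the written rule in 13.2.2 (2) is to continue.

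A reader might go further and infer that MSP is the wrong method, or that it inflates the trial because 165 and 231 PFS events exceed the fixed-design 138 and 194. The documents do not support that. MSP is a valid combination rule, adopted deliberately in version 2.0. The 738 patients follow from the OS calculation (492 for two arms, so 246 per arm), and the final PFS analysis is planned at 347 pooled events, more than the stand-alone calculations assume. Replacing MSP with another combination test would be a trade-off and is not needed to remove this fault.

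**Conclusion.** The bounds in 13.2.2 (2) are inconsistent. An interim P1 above 0.205 and up to 0.45 cannot succeed, yet the plan continues and permits enlargement. The probability is 24.5% with no effect, about 15% at HR 0.75 with 121 events, and 2% to 5.3% at HR 0.6 depending on the interim event count. Separately, the bracketed formula contradicts the stated cut-off; anyone applying it as written would test at 0.2724, with one-sided error of about 0.037 to 0.041 instead of 0.025.

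The loss of every later confirmatory test rests on P1 being the PFS1 comparison, which the section does not name. The 121-event figures rest on the assumed split. It might be inferred that the trial's type I error is inflated, but under the 0.2050 rule it is not. This should be fixed; it is not a fatal flaw.

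**What to change.** Keep MSP and set b1 = alpha2 = 0.205 in section 13.2.2 (2) and in the iDMC guideline, before any interim data are used. State that P1 and P2 are the stage-wise one-sided P values for PFS1, arm 1 versus control. The bracketed formula can then stay, since it equals 0.025 at the cut-off.

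The cost is a short amendment, with no extra patients and no change in power or type I error. The extra trials stopped (24.5% with no effect, about 2% to 5.3% at HR 0.6) are all ones that could not succeed. If the interim has already been used, b1 can no longer serve its purpose, but the 0.2050 cut-off should still be confirmed as the operative rule and the bracketed formula corrected before the final PFS test.

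### The bracketed adjusted-P formula for PFS contradicts the P1+P2 ≤ 0.2050 rule it is meant to restate; the formula is invalid below a sum of 0.45, while the cut-off itself controls the error

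*Protocol*

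**What the plan says.** Section 13.2.2 (1) of the protocol sets an overall one-sided level of 0.025 and puts the PFS comparison of intervention arm 1 with control (PFS1) first in a fixed sequence. Section 13.2.2 (2) then deals with the unblinded sample size re-estimation at 50% of the planned PFS events: "P values in two stages will be combined using the MSP". It gives a one-sided first-stage level α1 = 0.005; "the futility boundary is set as $b_1=0.45$ in the first stage"; and "the one-side significance level is set as $\alpha_2=0.2050$ in the secondary stage".

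The bullets send every trial with P1 ≤ 0.45 to the second stage, whether or not P1 is at or below α1, and stop for futility otherwise. After the second stage the test is P1+P2 ≤ α2. The bracket, opening with "that is, adjust P value", restates this as

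α1 + (P1+P2)(b1 − α1) − ½(b1² − α1²) ≤ 0.025,

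and when the condition is met "the between-group difference in PFS will be considered as statistically significant".

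No bullet says whether P1 ≤ α1 is itself a declaration of PFS significance. Section 13.2.2 (3), on OS, uses the same symbols α1, α2, P1 and P2 with other values, and defines P2 as "the one-side P value in the final analysis".

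**The concern.** The sentence offers two criteria as one. Substituting the plan's own numbers gives a negative P value exactly at the boundary where the formula should equal 0.025. A program written from the bracket and a reader applying the cut-off can therefore reach different conclusions on the same data.

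PFS1 opens the confirmatory sequence, so every later test depends on it. If the looser criterion were applied there, the familywise claim of 0.025 one-sided in section 13.2.2 (1) would no longer hold.

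**Working it through.** **Inputs**, all from section 13.2.2: α1 = 0.005, b1 = 0.45, α2 = 0.2050, target 0.025 one-sided. Assumption: under the null hypothesis the two stage-wise one-sided P values are independent and uniform, as the sum method requires.

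**1. The plan's cut-off is reproduced.** Let P1 ≤ α1 be a rejection. For α1 < P1 ≤ b1, reject if P1+P2 ≤ c. When c ≤ b1 this second region is a triangle with side c − α1, and the futility bound removes nothing. So

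error = α1 + ½(c − α1)² = 0.005 + ½(0.2050 − 0.005)² = 0.005 + 0.0200 = 0.0250.

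The 0.2050 is thus the exact solution under that reading.

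**2. Where the bracketed formula comes from.** When the sum s is at or above b1, the region is cut off at P1 = b1. Integrating (s − p) over p from α1 to b1 gives s(b1 − α1) − ½(b1² − α1²), which is the bracketed expression once α1 is added. It is right for s from b1 = 0.45 up to about 1. At s = 0.45 it meets the triangle form: 0.005 + 0.45×0.445 − 0.1012375 = 0.1040, and 0.005 + ½(0.445)² = 0.1040. Below 0.45 it does not apply, and the cut-off 0.2050 lies below 0.45.

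**3. The formula below 0.45.** Here ½(b1² − α1²) = ½(0.2025 − 0.000025) = 0.1012375.

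- At s = 0.2050: 0.005 + 0.2050×0.445 − 0.1012375 = −0.0050.
- It reaches zero at s = (0.1012375 − 0.005)/0.445 = 0.2163, so it is negative for every smaller sum.
- It reaches 0.025 at s = (0.025 − 0.005 + 0.1012375)/0.445 = 0.2724.

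With b1 = 0.2050 in place of 0.45 it would give 0.005 + 0.2050×0.200 − ½(0.042025 − 0.000025) = 0.0250. The expression therefore fits the cut-off only if b1 does not exceed α2.

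**4. An example.** P1 = 0.20 and P2 = 0.05 give s = 0.25.

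- Cut-off: 0.25 > 0.2050, not significant.
- Bracketed formula: 0.005 + 0.25×0.445 − 0.1012375 = 0.0150, significant.
- Correct adjusted P: 0.005 + ½(0.245)² = 0.0350 if P1 ≤ α1 rejects, or ½(0.25)² = 0.0313 if it does not. Both exceed 0.025.

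**5. Type I error of each criterion, one-sided.** If only the sum is tested, the error is c²/2. If P1 ≤ α1 also rejects, it is α1 + ½(c − α1)².

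| Criterion | Only the sum is tested | P1 ≤ 0.005 also rejects |
|---|---|---|
| P1+P2 ≤ 0.2050 | 0.0210 | 0.0250 |
| Bracketed formula ≤ 0.025 (P1+P2 ≤ 0.2724) | 0.0371 | 0.0408 |

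A simulation of 20 million pairs gave 0.0210, 0.0250, 0.0371 and 0.0407.

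**The case against.** The strongest defence is that the sum rule is the operative clause and the bracket only a gloss. The cut-off was derived correctly, so a statistician who applies it controls the error and the bracket does no harm. That stands as far as it goes: the excess error arises only if the formula is used. But the text presents the two as identical, and an adjusted P is what a program would compute and a report would print. The formula would also print negative values for the most convincing results.

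Three stronger readings are tempting and not supported.

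- *Neither criterion delivers 0.025.* The 0.2050 does deliver it if P1 ≤ 0.005 is a rejection. The section calls α1 a significance level and rules out only early stopping for PFS efficacy; it does not say that P1 ≤ α1 is non-significant. If the bullets are read as testing the sum alone, the result is 0.021, which is conservative and not a failure of control.
- *P2 is the cumulative P value at the final analysis.* That would give an error of about 0.073 for the 0.2050 rule with the interim at 50% information. The definition comes from the OS subsection, and the Figure S4 caption repeats it without tying it to PFS. The PFS subsection itself speaks of P values from two stages. What remains is reused notation that should be separated.
- *The cut-off should rise to √0.05 = 0.2236.* That is the value that spends the full 0.025 if only the sum is tested. It would make the first gate easier to pass and is a design choice, not a correction.

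**Conclusion.** The bracketed formula is wrong as written for the case it is used in. It is the expression for sums from 0.45 up to about 1, applied to a cut-off of 0.2050. The two stated criteria disagree for every sum between 0.2050 and 0.2724. Deciding by the formula would give a one-sided type I error of 0.037, about 48% above 0.025, or 0.041 if P1 ≤ 0.005 also rejects. The cut-off itself is correct or conservative (0.025 or 0.021), depending on a point the protocol leaves open.

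A reader might infer that the trial's PFS test ran at an inflated level. The document does not support that, since nothing in it shows which of the two criteria was applied. The non-equivalence is plain arithmetic on the plan's own values. The error rates rest on independent, uniform stage-wise P values. Because the conflict sits in the decision rule of the first confirmatory test, it has to be resolved.

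**What to change.** 1. Keep P1+P2 ≤ 0.2050 as the sole decision rule at the final PFS analysis for P1 between α1 and b1.
2. State whether P1 ≤ 0.005 is itself a declaration of PFS significance with the trial continuing. That is the reading under which 0.2050 gives 0.025. If it is not, say so and record that the rule is conservative at 0.021.
3. Replace the bracket. For α1 < P1 ≤ b1 and P1+P2 ≤ b1, use adjusted P = α1 + ½(P1+P2−α1)². Keep the present expression only for sums from b1 = 0.45 up to about 1. If P1 ≤ 0.005 is not a rejection, use (P1+P2)²/2 for sums up to b1. Give the range of validity with each formula, since neither quadratic form holds above 0.45.
4. State that P1 and P2 for PFS are the independent P values of the two stages, and give them and their boundaries symbols distinct from those for OS in section 13.2.2 (3).

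The cost is a few lines of text and a change to the program that computes the adjusted P. The cut-off, the futility boundary, the event numbers and the test sequence stay as they are.
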